## SUMMARY

**Rationale:** Antithrombotic therapy carries high risks for patient safety. The Dutch HARM study showed that antithrombotics belong to the top 5 of medication involved in potentially preventable HARMs. Multidisciplinary teams have been proposed to improve the safety of antithrombotic therapy. However, most antithrombotic services are described mainly as pharmacist-led antithrombotic services in US hospitals that are predominantly aimed at warfarin dosing, which differs from the Dutch situation. At present the effect of a multidisciplinary antithrombotic team in the Dutch situation is unknown. The hypothesis is that the introduction of a multidisciplinary antithrombotic team (in Dutch 'Stollingsteam' or S-team) in hospital will improve the efficacy and safety of antithrombotic therapy.

**Objective:** The main objective of this study is to determine the effect of a multidisciplinary antithrombotic team ('S-team') on the frequency of a composite endpoint consisting of bleeding and thrombotic events. The secondary objectives are to study the effect of a S-team on the frequency of bleeding events, frequency of thrombotic events, severity of bleeding complications, length of hospital stay, readmissions, quality of life, adherence by the patient to the therapy, quality of care (patient satisfaction with antithrombotic therapy), adherence by the doctors to the hospital protocol, healthcare costs, all-cause mortality and percent time in therapeutic range of vitamin K antagonists.

**Study design:** An intervention study with a before- and after design.

**Study population:** Patients that are or will be treated with antithrombotics during admission to the university medical center Erasmus MC Rotterdam or general teaching hospital Reinier de Graaf Ziekenhuis Delft are included in the study. We aim to include 1834 patients, 917 patients in the pre-intervention phase and 917 patients in the post-intervention phase.

**Intervention:** The intervention consists of the implementation of the S-team.

**Main study parameters/endpoints:** Proportion of patients with a composite endpoint consisting of  $\geq 1$  bleeding (major bleeding and mild to moderate clinically relevant non-major bleeding) or  $\geq 1$  thrombotic event from time to start with antithrombotic medication (or hospitalization) until 3 months after hospitalization.

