### 4.2 Inclusion criteria

In order to be eligible to participate in this study, a subject must meet all of the following criteria:

- Patients that are or will be treated with antithrombotics in the Erasmus MC or in the Reinier de Graaf hospital.
- Informed consent (we will ask permission from the patients to collect community pharmacy and to fill out four questionnaires).
- Only the first hospital admission of a patient within the study period will be included (readmission is an endpoint).

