### 4.3 Exclusion criteria

A potential subject who meets any of the following criteria will be excluded from participation in this study:

- No informed consent
- Patients admitted for one day
- Patients admitted to the Intensive Care Unit
- Patients treated with low molecular weight heparins monotherapy for thrombosis prophylaxis
- Patients enrolled in a clinical trial of antithrombotic therapy
- Patients treated with phytomenadione used for the prevention and treatment of vitamin K deficiency
- Patients treated during hospitalization with a single dose of the antithrombotic agents

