### 8.3.1 Pre-intervention phase

During a 9-month period usual care is provided to patients. This means that antithrombotic therapy, related patient instructions and handover after discharge are carried out by the physicians responsible for the patient. Patients that are or will be treated with antithrombotics in the Erasmus MC and in the Reinier de Graaf hospital will be included with the help of a clinical rule. The criteria on which the clinical rule screens are the use of antithrombotic drugs which are listed in table 1 and the use of antidotes which are listed in table 2.

Table 1: Antithrombotic agents

| Group of antithrombotic agents (ATC code) | Antithrombotic agents (ATC code) |
|-------------------------------------------|----------------------------------|
| Vitamin K antagonists (B01AA)             | Phenprocoumon (B01AA04)          |
|                                           | Acenoucoumarol (B01AA07)         |
| Heparin group (B01AB)                     | Heparin (B01AB01)                |
|                                           | Antithrombin III (B01AB02)       |
|                                           | Dalteparin (B01AB04)             |
|                                           | Enoxaparin (B01AB05)             |
|                                           | Nadroparin (B01AB06)             |
|                                           | Danaparoid (B01AB09)             |
|                                           | Tinzaparin (B01AB10)             |
| Direct thrombin inhibitors (B01AE)        | Bivaluridin (B01AE06)            |
|                                           | Dabigatran etexilate (B01AE07)   |
| Direct factor Xa inhibitors (B01AF)       | Rivaroxaban (B01AF01)            |
|                                           | Apixaban (B01AF02)               |
| Other antithrombotic agents (B01AX)       | Fondaparinux (B01AX05)           |

Table 2: Antidotes

| Group of antihemorrhagics (ATC code) | Antihemorrhagics (ATC code)                                   |
|--------------------------------------|---------------------------------------------------------------|
| Amino acids (B02AA)                  | Tranexamic acid (B02AA02)                                     |
| Vitamin K (B02BA)                    | Phytomenadione (B02BA01)                                      |
| Fibrinogen (B02BB)                   | Fibrinogen, human (B02BB01)                                   |

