|                | Length*                                                                                                                                                                                                                                               |
|                | Community pharmacist**\$                                                                                                                                                                                                                              |
|                | Reason for hospitalization*                                                                                                                                                                                                                           |
|                | Reason for exclusion                                                                                                                                                                                                                                  |
|                | (Co)morbidity*                                                                                                                                                                                                                                        |
|                | Day of hospitalization*                                                                                                                                                                                                                               |
|                | Any surgery (coded with Verrichtingen code  ) or diagnosis during hospitalization*                                                                                                                                                       |
| Study outcomes | Bleeding (major bleeding and mild to moderate clinical relevant non-major bleeding) or thrombotic event during hospitalization*                                                                                                                       |
|                | Bleeding (major bleeding and mild to moderate clinical relevant non-major bleeding) or thrombotic event within 3 months after hospitalization^                                                                                                        |

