|                 | Overview of medication use three months after hospitalization (coded with ATC-code  )+                                                                                                                                                                                                                                                                                                                                                                                                                                                                                                                                        |

\*Obtained from medical record of the hospital information system

+Obtained from the community pharmacist and the Thrombosis Service

\$Obtained from the patient using questionnaire

^Obtained by sending a small questionnaire asking for visits to the general practitioner or hospital because of a bleeding or thrombotic event within 3 months after hospitalization.

***The primary outcome of the study is the proportion of patients with a composite endpoint consisting of  $\geq 1$  bleeding (major bleeding and mild to moderate clinical relevant non-major bleeding) or  $\geq 1$  thrombotic events during and 3 months after hospitalization.***

Patients treated with antithrombotics and/or antidotes in the Erasmus MC and in the Reinier de Graaf hospital will be included with the help of a clinical rule (table 1 and 2). The data from the medical record of the hospital information system is used to determine whether there is a bleeding (major bleeding and mild to moderate clinical relevant non-major bleeding) or thrombotic event in patients who are enrolled in the study.

After hospitalization data from community pharmacist, general practitioner and the Thrombosis Services are used. At discharge the patient will be asked to fill in a consent form. By signing the consent form, the patient gives permission to retrieve patient data from the community pharmacist, general practitioner and the Thrombosis Services.

Definition of terms:

The ISTH definitions of bleeding in patients are as follows:

- Major Bleeding in non-Surgical Patients
  - 1. Fatal bleeding, and/or
  - 2. Symptomatic bleeding in a critical area or organ, such as intracranial, intraspinal, intraocular, retroperitoneal, intra-articular or pericardial, or intramuscular with compartment syndrome, and/or

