  - 3. Bleeding causing a fall in hemoglobin level of  $20 \text{ g L}^{-1}$  ( $1.24 \text{ mmol L}^{-1}$ ) or more, or leading to transfusion of two or more units of whole blood or red cells.
- Major bleeding in surgical patients
  - 1. Fatal bleeding, and/or
  - 2. Bleeding that is symptomatic and occurs in a critical area or organ, such as intracranial, intraspinal, intraocular, retroperitoneal, pericardial, in a non-operated joint, or intramuscular with compartment syndrome, assessed in consultation with the surgeon, and/or
  - 3. Extrasurgical site bleeding causing a fall in hemoglobin level of  $20 \text{ g L}^{-1}$  ( $1.24 \text{ mmol L}^{-1}$ ) or more, or leading to transfusion of two or more units of whole blood or red cells, with temporal association within 24–48 h to the bleeding, and/or
  - 4. Surgical site bleeding that requires a second intervention (open arthroscopic, endovascular) or a hemarthrosis of sufficient size as to interfere with rehabilitation by delaying mobilization or delayed wound healing, resulting in prolonged hospitalization or a deep wound infection, and/or
  - 5. Surgical site bleeding that is unexpected and prolonged and/or sufficiently large to cause hemodynamic instability, as assessed by the surgeon. There should be an associated fall in hemoglobin level of at least  $20 \text{ g L}^{-1}$  ( $1.24 \text{ mmol L}^{-1}$ ), or transfusion, indicated by the bleeding, of at least two units of whole blood or red cells, with temporal association within 24 h to the bleeding.

- Mild to moderate bleeding:
  - o All bleeding events that do not meet the International Society of Thrombosis and Haemostasis (ISTH) criteria according to which major bleeding is defined.

Thrombotic event: any arterial or venous thrombosis, including acute myocardial infarction or stroke for arterial thrombosis and deep venous thrombosis or pulmonary embolism for venous thrombosis.

Definition of terms:

- Acute myocardial infarction: Detection of a rise and/or fall of cardiac biomarker values [preferably cardiac troponin (cTn)] with at least one value above the 99th percentile upper reference limit (URL) and with at least one of the following:
  - o Symptoms of ischemia
  - o New or presumed new significant ST-segment–T wave (ST–T) changes or new left bundle branch block (LBBB).
  - o Development of pathological Q waves in the ECG.

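### No index time is fixed for the LMWH exclusion or the at-risk window, so a clot arising in hospital can both make a patient eligible and count as a primary event

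*Protocol*

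**What the plan says.** **Eligibility.** Section 4.2 includes "Patients that are or will be treated with antithrombotics in the Erasmus MC or in the Reinier de Graaf hospital". It limits neither the indication nor the timing of treatment relative to an event. Section 4.3 excludes "Patients treated with low molecular weight heparins monotherapy for thrombosis prophylaxis" and names no time at which this is assessed.

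**Case finding and consent.** Section 8.3.1 states: "The criteria on which the clinical rule screens are the use of antithrombotic drugs which are listed in table 1". Table 1 includes the LMWHs. The rule also screens on the antidotes in Table 2. On consent, 8.3.1 says: "At discharge the patient will be asked to fill in a consent form". Neither step fixes eligibility before an in-hospital event.

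**Endpoint window.** The Summary and 8.1.1 run it "from time to start with antithrombotic medication (or hospitalization) until 3 months after hospitalization". The restatement of the primary outcome in 8.3.1 refers instead to "thrombotic events during and 3 months after hospitalization", which covers the whole stay.

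**Event definition and data.** The definition in 8.3.1 begins "Thrombotic event: any arterial or venous thrombosis" and makes no exception for the event that prompted treatment. Table 3 lists a bleeding "or thrombotic event during hospitalization" as an outcome. It lists neither an onset date for the event nor a start date for the qualifying drug.

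**The concern.** Take two patients on prophylactic LMWH alone. The first has no clot and is excluded. The second develops a DVT in hospital and is started on treatment. This patient is no longer on prophylactic monotherapy, fits 4.2, and has the DVT inside the stay. A patient on no antithrombotic who is treated for a clot arising in hospital can enter in the same way through the hospitalization branch of the window.

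For patients who enter like this, eligibility is a consequence of the outcome, and all of them have an event. The primary and thrombotic proportions then mix a risk among treated patients with a count of clots from a group whose clot-free members are not observed. The intervention acts on patients whom the drug-triggered rule presents to the S-team (8.3.3), so its patient-level review cannot prevent a clot that preceded the qualifying order. If the number of such entrants changes between phases, the study has no denominator with which to see why.

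The point concerns clots arising after admission, not the event that caused the admission.

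**Working it through.** **1. Can the route occur under the text?**

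| Step | Source | Does the text prevent it? |
|---|---|---|
| Prophylaxis-only or untreated patient clots in hospital and is treated | 4.2, 4.3 | No: no time point, no limit on indication |
| Patient is found and asked for consent | 8.3.1 | No: found by drug use, asked at discharge |
| Clot lies in the window | Summary, 8.1.1, 8.3.1 | Not under the hospitalization or whole-stay wording. Under the start-of-medication wording it depends on which drug starts the clock |
| Clot meets the definition | 8.3.1 | No: no exception for the triggering event |

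**2. Reproduce the planned sample size.** Inputs from 4.4: 9% vs 5.5%, alpha 0.05, power 0.80. With Δ = 0.035 and mean rate 0.0725:

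- Uncorrected: n = [1.960·√(2·0.0725·0.9275) + 0.842·√(0.09·0.91 + 0.055·0.945)]² / 0.035² = 860.5, or 861.
- Continuity-corrected: (n/4)·[1 + √(1 + 4/(nΔ))]² = 916.8, or **917**, which matches 4.4.

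The plan's figure is therefore two-sided with continuity correction and is correct on its own inputs.

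**3. Equal numbers of event-only entrants in both phases.** Let k of the 917 patients per phase enter through their clot, with the rest at the planned rates:

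p1 = [k + 0.09(917 − k)]/917 and p2 = [k + 0.055(917 − k)]/917.

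The protocol gives no k. As an assumption, 500 to 4,000 prophylaxis-only patients per phase with a 0.25% to 1% in-hospital clot risk give k from 500 × 0.0025 ≈ 1 to 4,000 × 0.01 = 40. Power uses the same corrected formula, that is, effective size (917Δ − 1)²/(917Δ²) with Δ = p1 − p2.

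| k | p1 | p2 | Relative risk | Power, corrected | Power, uncorrected |
|---|---|---|---|---|---|
| 0 | 9.0% | 5.5% | 0.61 | 0.80 | 0.82 |
| 1 | 9.1% | 5.6% | 0.62 | 0.79 | 0.82 |
| 5 | 9.5% | 6.0% | 0.63 | 0.77 | 0.80 |
| 15 | 10.5% | 7.1% | 0.67 | 0.71 | 0.74 |
| 30 | 12.0% | 8.6% | 0.72 | 0.64 | 0.67 |
| 40 | 13.0% | 9.6% | 0.74 | 0.59 | 0.62 |

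The absolute difference barely moves (3.50 to 3.35 points). Power falls because the variance rises.

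**4. Unequal numbers and no S-team effect (9% in the rest of both phases).** Rejection probability of the plain two-sided comparison without continuity correction, nominal 0.05:

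| Entrants, pre vs post | Rates | Binomial sampling | k held fixed |
|---|---|---|---|
| 10 vs 5 | 10.0% vs 9.5% | about 0.06 | about 0.06 |
| 15 vs 10 | 10.5% vs 10.0% | about 0.06 | about 0.05 |
| 30 vs 15 | 12.0% vs 10.5% | 0.17 | about 0.14 |

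**The case against.** **The exclusion may already close the main route.** Section 4.3 can be read as removing anyone who received LMWH alone for prophylaxis at any time in the stay. A reader might infer that the protocol excludes such patients unless they clot. It states no such rule, and that reading is not supported. What stands is that the text does not choose, so two hospitals and two phases could apply it differently. Even the strict reading leaves open the route for patients on no antithrombotic.

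**The window may start at the qualifying drug.** The wording in the Summary and 8.1.1 can mean hospitalization for patients already treated and otherwise the start of the qualifying drug. A clot before that drug is then outside the window. This is close to the fix below, but the whole-stay wording in 8.3.1 contradicts it.

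**Entry does not require a clot.** Any added or switched antithrombotic ends prophylactic monotherapy, so event-free patients also come in. It would be wrong to say that this group supplies only events. Only the clot-triggered subset has a 100% event rate.

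**The size is unknown and may be small.** A reader might suppose the group is large, but the protocol has no figure. Three features push k down. Consent at discharge removes patients who die in hospital. ICU admission is an exclusion. The 917 may be a subset of those eligible: 4.4 implies 3,800 × 9/48 ≈ 713 VKA users in nine months at one hospital, before the other hospital and other drugs are added.

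**Bias is not established.** A reader might infer an inflated false-positive rate. The 0.17 needs the entrants to halve from 30 to 15. Section 10.1 also names interrupted time series and multivariate logistic regression, and S-team guidelines and education might themselves change hospital-acquired clots. This objection stands. None of it restores the missing denominator, however.

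**Table 3 is a content summary.** Medication use during the stay is collected from the hospital record, so absent date fields are weak evidence taken alone.

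**Conclusion.** The point holds as a defect of definition. The protocol fixes neither when the prophylactic-LMWH exclusion is judged nor a single start of the at-risk window. Its wording therefore permits an event that triggers qualifying treatment to count as a primary event. This decides which patients and events make up the primary proportion, and eligibility and endpoint timing are matters that the protocol itself sets.

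The size rests entirely on an assumed k. At 1 to 5 entrants per phase the loss is small (power 0.79 to 0.77). At 40 it is material (0.59). Equal numbers raise both rates and dilute the contrast. Bias needs a difference between phases, and the documents give no reason to assume one. The planned sample size is not in error. The change should be made, but the finding does not show that the comparison is invalid.

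**What to change.** - **Index time.** In 4.3 and 8.1.1 define one index time per patient: admission if the patient is already on a qualifying antithrombotic, otherwise the first qualifying order in that stay. State when the LMWH exclusion is judged, and that prophylactic LMWH monotherapy does not start the window.
- **One window.** Reconcile the restated primary outcome in 8.3.1 with 8.1.1.
- **Counting rule.** Count only events with onset after the index time, so that the event prompting the qualifying order is not an endpoint event. Apply the same principle to bleeds in patients identified only by antidote use.
- **Data.** Add the qualifying-order date and the event onset date to Table 3, collected identically in both phases.

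The cost is protocol wording and two dates read from the hospital record, with no extra patients or procedures. The downside is fewer counted events. Those lost include the events that created their own eligibility.

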### 4.4 Sample size calculation

In studies major bleeding complications tend to occur in about 2-3% of all patients per year on antithrombotics, but in every day practice it seems this rate is at least 10%. Conservatively, we will presume a rate of 5%. Thrombotic events are estimated to occur in 3% of treated patients per year in studies. As trials form the ideal situation, we assume this is the rate we could achieve with the S-team and that the rate is 4% in the pre-intervention period. This results in a composite rate of 9% and we expect to decrease this to 2.5% bleeding events and 3% thrombotic events (composite 5.5%). With an alpha of 0.05 and power of 0.80 the required sample size will be 917 patients in the pre-intervention phase and 917 patients in the post-intervention phase. In order to account for drop-outs 1900 patients will be included.

In a (not yet published) study aiming at the development of a prediction rule for VKA-related International Normalized Ratio (INR) elevation from our Erasmus MC group 3800 patients using VKAs were included over 4 years. Thus within 9 months over 700 patients using VKAs will be admitted to the Erasmus MC alone. As we include another hospital and other antithrombotics as well, we expect that 9 months will be sufficient to recruit the required number of patients.

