## 8. METHODS

### 8.1 Study parameters/endpoints

#### 8.1.1 Main study parameter/endpoint

Composite endpoint: proportion of patients with  $\geq 1$  bleeding (major bleeding and mild to moderate clinically relevant non-major bleeding) or  $\geq 1$  thrombotic events from time to start with antithrombotic medication (or hospitalization) until 3 months after hospitalization.

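### The planning rates of 9% and 5.5% come from per-year rates of major bleeding and thrombosis, but the endpoint covers the stay plus 3 months and adds non-major bleeding, so the 80% power is unsupported

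*Protocol*

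**What the plan says.** Protocol section 4.4 builds the planning rates in three steps.

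- **Bleeding.** It reports that in studies "major bleeding complications tend to occur in about 2-3% of all patients per year on antithrombotics". It adds that "in every day practice it seems this rate is at least 10" per cent, and then: "Conservatively, we will presume a rate of 5" per cent.
- **Thrombosis.** "Thrombotic events are estimated to occur in 3% of treated patients per year in studies". This 3% becomes the post-intervention rate unchanged, and 4% is assumed for the pre-intervention phase.
- **Composite.** "This results in a composite rate of 9% and we expect to decrease this to 2.5% bleeding events and 3% thrombotic events", which sums to 5.5%.

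It continues: "With an alpha of 0.05 and power of 0.80 the required sample size will be 917 patients in the pre-intervention phase", with the same number in the post-intervention phase. The total of 1834 is raised to 1900 for drop-outs.

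Section 8.1.1 defines the primary endpoint as the proportion of patients with at least one bleeding or thrombotic event, counted "from time to start with antithrombotic medication (or hospitalization) until 3 months after hospitalization". Bleeding there means major bleeding plus mild to moderate clinically relevant non-major bleeding. The summary and section 8.3.1 agree with this.

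**The concern.** The planning rates differ from the endpoint in two ways. The time unit is a year, whereas the endpoint window is the stay plus about a quarter of a year. The bleeding rate is for major bleeding, whereas the endpoint also counts clinically relevant non-major bleeding. Section 4.4 converts neither, and the protocol gives no 3-month rate and no non-major bleeding rate.

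This calculation is the only justification of the sample size. If the composite risk over the window were near 2-3%, few events would be expected, and a null result could be misread as evidence that the S-team has no effect. If non-major bleeding is common, power could be adequate. The plan does not let a reader tell which.

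**Working it through.** **Inputs.** From 4.4: bleeding 5% to 2.5%, thrombosis 4% to 3%, composite 9% to 5.5%, 917 per phase, alpha 0.05, power 0.80. Sidedness is not stated; two-sided is taken because only that reproduces 917. The 5%, 4% and 2.5% carry no time unit of their own. They are read as annual because 4.4 sets them against per-year figures and offers no other unit.

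**Step 1: reproduce 917.** With p̄ = (p1 + p2)/2 and d = p1 − p2,

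n = [1.96·√(2p̄(1−p̄)) + 0.842·√(p1(1−p1) + p2(1−p2))]² / d²

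For p1 = 0.09 and p2 = 0.055: (0.7188 + 0.3079)² / 0.035² = 861. The continuity correction, n/4·[1 + √(1 + 4/(n·d))]², gives 917, an exact match. The one-sided versions give 678 and 734.

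**Step 2: scale time only.** The stay is not quantified in 4.4, so windows of 91 to 121 days are assumed (3 months, up to about 4 months). With t = days/365, the risk is p·t (linear) or 1 − (1−p)^t (exponential). Both assume a constant hazard. Power at 917 per phase is

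Φ[(d − 1.96·√(2p̄(1−p̄)/917)) / √((p1(1−p1) + p2(1−p2))/917)]

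This version has no continuity correction. For 9% vs 5.5% it gives 82%, so it is slightly generous compared with the plan's own formula.

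| Window | Scaling | Pre | Post | Expected events in 917 | Power |
|---|---|---|---|---|---|
| as planned | none | 9% | 5.5% | 83 vs 50 | 82% |
| 91 days | linear | 2.24% | 1.37% | 21 vs 13 | 29% |
| 91 days | exponential | 2.32% | 1.40% | 21 vs 13 | 31% |
| 121 days | linear | 2.98% | 1.82% | 27 vs 17 | 37% |
| 121 days | exponential | 3.08% | 1.86% | 28 vs 17 | 39% |

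Using all 1900 patients (950 per phase) gives 30-32% at 3 months, so the drop-out allowance changes little.

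**Step 3: the plan's higher bleeding figure.** Take bleeding at 10% per year, assumed halved to 5%, with thrombosis 4% to 3%: 14% vs 8% per year. With linear scaling:

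- 91 days: 3.49% vs 1.99%, power 50%.
- 121 days: 4.64% vs 2.65%, power 62%.

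**Step 4: allow for non-major bleeding.** Suppose total bleeding is k times the presumed 5% and is also halved (assumption). The annual rates are then 5k + 4 vs 2.5k + 3 per cent. Power at 917 per phase, linear scaling:

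| k | 91 days | 121 days |
|---|---|---|
| 1 | 29% | 37% |
| 2 | 50% | 62% |
| 3 | 67% | 80% |
| 4 | 80% | 90% |

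Starting from 10% per year, total bleeding at twice that rate gives 80% at 91 days and 90% at 121 days.

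**The case against.** The strongest reply is that the two mismatches pull in opposite directions. A shorter window lowers the risk, and counting non-major bleeding raises it. Section 8.3.1 defines mild to moderate bleeding broadly, as any bleeding that fails the ISTH major criteria, although 8.1.1 limits it to clinically relevant events. So k = 1 is a floor, not a central estimate. The plan also calls 5% conservative next to a figure of at least 10%. Finally, the window opens at admission or treatment start in hospital patients, some of them surgical. If events cluster there, a constant hazard understates the 3-month risk.

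All of this stands against a stronger reading. A reader might infer that 80% power is not delivered, that the trial is badly underpowered, or that its true power is about 30%. The documents do not support that. The 29-39% corrects the time unit only and keeps bleeding at major bleeding, so it is not the power for the endpoint in 8.1.1. That power cannot be computed from the protocol.

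The reply does not rescue the 80%. Section 4.4 makes none of these arguments, gives no non-major bleeding rate or in-hospital rate, and does not say that the S-team is expected to reduce non-major bleeding equally. Two unacknowledged mismatches that might cancel do not justify the figure.

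**Conclusion.** The point holds in this form: the 80% power at 917 per phase is unsupported, because 9% and 5.5% do not describe the endpoint in either duration or event definition. The arithmetic from those inputs is correct.

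On size, correcting time alone lowers power to 29-39%, or about 50-62% with the plan's 10% bleeding figure assumed halved. Total bleeding of about 3-4 times the presumed 5%, also halved, would restore about 80%. These ranges rest on the annual reading of the 5%, 4% and 2.5%, a constant hazard, a window of 91-121 days and a two-sided test. The mismatch itself is certain from the text. How much power is lost, if any, is not.

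**What to change.** Rewrite section 4.4 as follows.

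1. State the expected risk, before and after, of the full composite (major or clinically relevant non-major bleeding, or thrombosis) over the stay plus 3 months.
2. Give the assumed non-major bleeding rate, its source and the effect expected on it, and say how yearly rates were converted to the window.
3. Show the power and the detectable difference that 917 per phase gives over a range of such risks. Do not enter 30% as the power for the full composite, because that would repeat the mismatch in event definition.
4. Once pre-intervention follow-up is complete, update that statement with the observed pre-intervention composite risk.

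The cost is a recalculation and protocol wording, with no extra patients or procedures. The downside is that the stated power may become less favourable.
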